## Abstract

**Background:**

Dysphagia is as a common consequence of cerebral infarction affecting approximately 50% of stroke patients. It often results in aspiration pneumonia, malnutrition and dehydration. Dysphagia is also seen after mechanical manipulation of the larynx, for example after prolonged intubation and after the perioperative use of transesophageal echocardiography (TEE). TEE is a semi-invasive procedure assessing the function of the intra-atrial septum and heart valves, yielding more detailed results compared to transthoracic echocardiography (1). It has become a routine in the diagnostic work-up of stroke. The study *Transoesophageal echocardiography: dysphagia risk in the acute phase after stroke* (*TEDRAS study*) was the first to investigate the extent of dysphagia risk after TEE in acute stroke patients. The trial findings supported the hypothesis that dysphagia severity worsens following TEE. This follow-up trial is designed to address the limitations of the first TEDRAS study, focusing on patients with ischaemic stroke and transient ischemic attack (TIA).

**Methods:**

The study is a prospective, single-blinded, controlled pilot trial, designed in accordance with the SPIRIT reporting guidelines. The study protocol outlines that both FEES and TEE will be performed on patients with acute ischaemic stroke or transient ischemic attack (TIA) who provide informed consent to participate. Specifically, the following parameters are to be analyzed in both groups: (1) The impact of the type and method of anaesthesia administration (intravenous vs. local anesthetic spray application) during TEE on swallowing function in both cohorts; (2) The effect of the duration of the TEE procedure on swallowing function in both cohorts; (3) The experience level of the TEE examiner; (4) The interrater reliability of the FEES assessment. The trial will be conducted at the University Medical Centre of the Justus-Liebig-University in Giessen (UKGM) through collaboration between the Departments of Neurology and Cardiology of the UKGM.

**Discussion:**

This protocol presents a prospective pilot single-blinded controlled study designed to assess further risks of dysphagia following TEE. The trial aims to address several outcomes, specifically the impact of anaesthesia and the duration of TEE on swallowing, which will be correlated with the severity of dysphagia after TEE.

**Trial registration:**

ClinTrial.gov Identifier NCT04302883.

URL: https://clinicaltrials.gov/study/NCT06195501?term=TEDRAS&rank=1

Registered June 2024.

## Administrative information

**Table Taba:** 

Title and structured summary	(1a) TEDRAS II - Transesophageal Echocardiography as Dysphagia Risk in the Acute phase of Stroke - protocol for a prospective pilot observational trial (1b) This pilot follow-up trial is designed to address the impact of the duration of TEE on swallowing in acute stroke patients and patients with transient ischemic attack, the type of anesthesia as well as the inter- and intrarater reliability for FEES. We will specifically analyse the following parameters in both groups: 1) The impact of the type and method of anaesthesia administration (intravenous vs. local anesthetic spray application) during TEE on swallowing function in both cohorts. 2) The effect of the duration of the TEE procedure on swallowing function in both cohorts. 3) The experience level of the TEE examiner. 4) The interrater reliability of the FEES assessment. The study is a pilot prospective, single-blinded, controlled trial, designed in accordance with the SPIRIT reporting guidelines. The study protocol outlines that both FEES and TEE will be performed on patients who provide informed consent to participate. Patients with acute ischemic stroke or TIA that provided their consent to participate are included in the trial.
Protocol version	(2) Protocol version #1, TEDRAS 2 June 2024
Roles and responsibilities	(2) **Names:** [name]^1, 3^ [name]^1^ [name]^1^ [name]^2^ [name]^2^ [name]^2^ [name]^1,5^ [name]^1^ [name]^4^ [name]^1^ [name]^1^ **Affiliations:** ^1^University Hospital Giessen and Marburg, Campus Giessen, Department of Neurology, Giessen, Germany ^2^University Hospital Giessen and Marburg, Campus Giessen, Department of Cardiology, Giessen, Germany ^3^Swiss University of Speech Therapy - hlo, St. Gallen, Switzerland ^4^Kerckhoff-Clinic, Heart & Brain Research Group, Bad Nauheim, Germany ^5^Die Neurologen, Private Neurology Practice, Bad Nauheim, Germany **Roles:** Principal investigator: [name] Key clinical investigators: [name], [name], [name], [name], [name], [name], [name] Independent experts: [name], [name], [name]

## Background

Dysphagia is as a common consequence of cerebral infarction, affecting at least 50% of stroke patients [1]. It often results in aspiration pneumonia, malnutrition and dehydration which are considered the most important secondary complication on the stroke unit [2]. Up to 50% of stroke patients suffer dysphagia 6 months from experiencing an ischaemic stroke [3]. Additionally, dysphagia causes numerous other secondary complications [4–6], contributing to substantial healthcare cost [7–9]. 

Dysphagia involves a complex pattern of swallowing dysfunction; the aetiology is heterogeneous [10]. The oropharynx is a highly sensitive structure transmitting information about the composition of the bolus to the cortex. Proper function of the tongue and muscles of the mouth floor is crucial for bolus formation and expulsion. In the hypopharynx, pressure dynamics and the contraction force of the pharyngeal muscles are essential for bolus expulsion into the oesophagus [11]. Damage to the muscles or nerves in this area can result in serious swallowing dysfunctions, increasing the risk of aspiration.

The complex protective mechanism of the upper airway during swallowing must operate precisely to protect the airway as the bolus is propelled into the oesophagus. Injuries or surgical interventions involving the hypopharynx and larynx are particularly critical. Dysphagia is commonly seen after prolonged intubation [12–14] and has been reported after the perioperative use of transoesophageal echocardiography (TEE) [15].

TEE, a semi-invasive procedure, provides enhanced visualization of the heart’s structure and function, particularly for assessing the intra-atrial septum and heart valves, often yielding more detailed results compared to transthoracic echocardiography [16]. It plays a crucial role in the diagnostic work-up of ischaemic stroke, particularly in identifying cardioembolic sources such as left atrial appendage thrombus (LAAT) and spontaneous echo contrast (SEC). Recent studies have demonstrated that TEE provides prognostically significant findings even in anticoagulated patients with atrial fibrillation (AF), where the CLOTS-AF score (*C*reatinine levels > 1.5 mg/dL (2 points), *L*VEF < 50% (2 points), LAVI > 34 mL/m^2^ (indicatingng *O*verload, 1 point), *T*APSE < 17 mm (2 points), history of prior **s**troke (3 points) and presence of *AF* rhythm (2 points). The total score can range from 0 to 12 points and has shown superior predictive accuracy for LAAT compared to conventional risk scores [17–20]. Moreover, TEE has revealed a substantial prevalence of thrombus in stroke patients without documented AF, highlighting the importance of structural cardiac abnormalities as embolic sources. These findings underscore the value of TEE in refining risk stratification and guiding secondary stroke prevention, especially in patients with cryptogenic or embolic strokes of undetermined source (ESUS).

While it is generally considered a minimal invasive and safe procedure, complications such as mucosal injuries, bleeding in the upper gastrointestinal tract or aspiration pneumonia can still occur. In relation to swallowing, injuries to the oesophagus, larynx or pharynx may contribute to dysphagia [21–23]. The duration of the TEE procedure may also influence these risks [24].

Professional and effective dysphagia management and successful rehabilitation after stroke depend on targeted and standardized imaging diagnostics to assess both symptoms and underlying pathomechanisms. In Germany, Flexible Endoscopic Evaluation of Swallowing (FEES) has become the most widely used imaging tool for diagnosing dysphagia [25]. Since the introduction of the FEES curriculum by the German Society of Neurology (DGN) and the German Stroke Association (DSG) in 2014 [26], this imaging method has been implemented in 70% of stroke units across the country [25].

The procedure is performed by inserting a flexible videoendoscope, approximately 3 mm in diameter, through the lower nasal passage into the hypopharynx. FEES is video recorded, with playback capabilities of 25–50 frames per second, allowing precise identification of key symptoms and pathomechanisms. It can be performed at the patient’s bedside, even in challenging conditions, and repeated as often as required. This diagnostic tool is considered low-risk: a trial of 300 acute stroke patients reported no significant changes in cardiorespiratory parameters, no laryngospasm, vasovagal reaction, altered consciousness, or symptomatic bradycardia or tachycardia during the procedure [27].

The study *Transoesophageal echocardiography: dysphagia risk in the acute phase after stroke* (*TEDRAS study*) approved by the ethics committee of the Justus Liebig University in Giessen (AZ.: 223/12; ClinTrial.gov Identifier NCT04302883) [28] was the first to investigate the extent to which TEE increases the risk of dysphagia in acute stroke patients. In this trial, patients with an acute ischaemic stroke were randomized into an intervention or a control group. The intervention group underwent FEES on 3 consecutive days, with the TEE taking place on the second day before the FEES. The control group also received FEES over 3 days, but TEE was performed only after the final FEES. The final findings supported the hypothesis that dysphagia severity worsens following TEE in the intervention group [28].

### Objectives

Building on the results of the initial TEDRAS trial, this follow-up trial is designed to address the limitations of the first TEDRAS study that were not sufficiently explored: The impact of the duration of TEE on swallowing, the type on anaesthesia as well as the interrater reliability for FEES. In the follow-up TEDRAS trial we will be focusing on patients with ischaemic stroke and transient ischemic attack (TIA) specifically analyzing the following parameters in both groups:The impact of the type and method of anaesthesia administration (intravenous vs. local anesthetic spray application) during TEE on swallowing function in both cohorts.The effect of the duration of the TEE procedure on swallowing function in both cohorts.The experience level of the TEE examiner.The interrater reliability of FEES.

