### Secondary outcomes

Comparison of TEE duration between patients with and without dysphagia and in cases of ischaemic stroke and TIA;Correlation between TEE duration and the degree of deterioration in FOIS-G and the experience of the TEE examiner in patients with ischaemic stroke and TIA;Correlation between TEE duration and TEE examiner’s experience in patients with ischaemic stroke and TIA;Interrater reliability in the evaluation of FEES.

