### Sample size estimation

Given the lack of existing data on the influence of anaesthesia type and form during TEE on swallowing in ischaemic stroke and TIA patients, this study is designed as a pilot trial. A total of 50 participants will be enrolled, with 25 patients in each group (stroke vs. TIA). The primary aim of this exploratory phase is to gather preliminary data to estimate effect sizes. These estimates will then serve as the basis for a formal power calculation and definitive sample size planning for a subsequent full-scale study.

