### Assignment of interventions: allocation

Since this is not a randomized trial the participants will be assigned to the aforementioned groups according to the diagnosis. The allocation sequence will be sequentially numbered by the allocating investigator MD and stored in a secure database only accessible by this person. The trial investigator responsible for enrollment and allocation will provide patients’s enrollment sequence number and allocate participants to respective groups after viewing the diagnosis. All enrolled patients will receive the same interventions in both groups.

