### Definition of dysphagia

Dysphagia is determined with the following cut-off values of the dysphagia scores:

Secretion Severity Rating Scale for Saliva Management (SSRS): SSRS ≥ 1; Penetration Aspiration Scale (PAS): PAS ≥ 3; Yale Pharyngeal Residue Severity Rating Scale: YS ≥ 3; Functional Oral Intake Scale (FOIS-G): FOIS-G < 7. Differences in patient-related data between the two groups: dysphagia/non-dysphagia group and intravenous vs. oral anaesthesia group are tested using Pearson’s chi-square test, Fischer’s exact test, *t*-test for independent samples or the Mann–Whitney *U*-test. For the purpose of logistic regression analyses, we intend to apply a median split to dichotomize the SSRS, PAS, YS and FOIS-G scores and create a binary outcome variable.

Assumptions for a *t*-test for independent samples are tested with the Levent test for variance homogeneity and the Shapiro–Wilk test including visual inspection of thedistribution plots for the assessment of normal distribution. If there is no homogeneity of variance or normal distribution, the Mann–Whitney *U* test for group differences is used. Correlations are calculated using the Pearson product-moment correlation or the Spearman rank correlation.

The inter-rater reliability between two raters is determined using a linearly weighted Cohen’s kappa, as this takes into account matches that could have arisen by chance on the one hand and places more weight on high non-matches on the other [39]. Furthermore, the percentage agreement and the Spearman rank correlation are specified for the agreement between two raters. In the case of a calculation of inter-rater reliability with more than two raters, a general agreement of all raters including subtraction of agreements by chance is calculated using Fleiss kappa [39].

Effect sizes are given according to Cohen’s d with a 95% confidence interval. *p*-values are given for all statistical results. The criterion for statistical significance is set at *p* < 0.05. Conclusions about clinically, practically and scientifically relevant correlations or differences are not made solely on the basis of the defined statistical significance [40].

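### The plan does not say whether anaesthesia and TEE-duration effects are estimated per cohort or pooled, and it names no diagnosis-adjusted effect and no stroke-versus-TIA difference in effect

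*Protocol article*

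**What the plan says.** Diagnosis is the only group structure that the design itself creates. Under Sample size estimation: "A total of 50 participants will be enrolled, with 25 patients in each group (stroke vs. TIA". Under Assignment of interventions: allocation: "Since this is not a randomized trial the participants will be assigned to the aforementioned groups according to the diagnosis". The same section says that both groups receive the same interventions.

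The Objectives introduce their list with "specifically analyzing the following parameters in both groups". The first two items, anaesthesia and TEE duration, repeat the reference to both cohorts; the anaesthesia item reads "during TEE on swallowing function in both cohorts". The Primary outcome names stroke and TIA patients together and does not say whether they are analysed jointly or separately.

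The analysis text, under Definition of dysphagia, tests "Differences in patient-related data between the two groups: dysphagia/non-dysphagia group and intravenous vs. oral anaesthesia group" with chi-square, Fisher, t or Mann–Whitney tests. It also announces logistic regression on median-split scores, without listing predictors. Diagnosis appears under Statistical methods as one of the patient-related data. The nearest text to a cohort comparison is a secondary outcome, "Comparison of TEE duration between patients with and without dysphagia and in cases of ischaemic stroke and TIA", which concerns a duration and not an effect on swallowing.

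**The concern.** The objectives and the sample are organised by diagnosis, but the named effect comparisons are not. The tests can be carried out in two ways, and neither serves the objectives well.

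- **Pooled without adjustment.** The cohort question goes unanswered. Since the trial is not randomised, any imbalance in anaesthesia form between stroke and TIA patients enters the anaesthesia comparison.
- **Separately in 25 patients each.** Each result is imprecise, and a contrast between one significant and one non-significant p-value can be mistaken for a difference in effect.

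What is at stake is the purpose given under Sample size estimation: "The primary aim of this exploratory phase is to gather preliminary data to estimate effect sizes". Whoever plans the full-scale study must know whether a reported Cohen's d is crude, diagnosis-adjusted or specific to one cohort.

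**Working it through.** **The plan's own figure.** 25 + 25 = 50, which is correct. The article gives no effect size, SD or power, so nothing further can be reproduced. For a pilot that is not a fault.

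**Inputs.** From the article: 25 patients per cohort, significance at p < 0.05, Cohen's d with 95% CI. Assumed: two-sided tests, no dropout, an anaesthesia split of 13:12 in each cohort (18:7 and 20:5 as alternatives), and true d of 0.3, 0.5 or 0.8. Mean comparisons in SD units stand in for the ordinal scores, so the figures are indicative.

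**Crude pooling.** If the cohorts differ by Δ SD in swallowing score, the bias in the crude anaesthesia difference is Δ × (stroke share in one anaesthesia group − stroke share in the other). As an illustration, take an 18:7 split in stroke, the reverse in TIA, and Δ = 1. The bias is 18/25 − 7/25 = 0.44 SD. With balanced anaesthesia there is no bias, but the SD is inflated: √(1 + 0.5²) = √1.25 = 1.118. The standardised effect then falls by 1 − 1/1.118 = 11%, and a sample size planned from it rises by 25%.

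**Separate tests.** The standard error per cohort is √(1/13 + 1/12) = 0.400 SD. Power p comes from the noncentral t distribution with 23 df and noncentrality d/0.400. If the effect is the same in both cohorts, P(exactly one significant) = 2p(1 − p).

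| True d | Power per cohort | Exactly one significant | Power, all 50 |
|---|---|---|---|
| 0.3 | 11% | 20% | 18% |
| 0.5 | 22% | 35% | 41% |
| 0.8 | 48% | 50% | 79% |

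At 18:7 the middle column is 18%, 31% and 48%; at 20:5 it is 16%, 27% and 45%. With no effect in either cohort it is 2 × 0.05 × 0.95 = 9.5%. A pattern in one named direction has half of each probability.

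**Precision (95% half-widths, 13:12).**
- Per cohort: 2.069 × 0.400 = 0.83 SD
- Combined: 2.011 × 0.400/√2 = 0.57 SD
- Difference between cohorts: 2.013 × 0.400 × √2 = 1.14 SD

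At 20:5 these become 1.03, 0.71 and 1.42 SD.

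**An interaction test.** If d is 0.8 in one cohort and 0 in the other, power is 28% (13:12), 24% (18:7) or 20% (20:5).

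**The case against.** A reader might infer that the plan will test each cohort separately and report an effect in stroke but not in TIA. The article does not support that. No section restricts a test to 25 patients, and the anaesthesia comparison carries no cohort restriction, so pooling all 50 is at least as natural a reading. No such conclusion is announced. The article also promises effect sizes with confidence intervals and says that conclusions will not rest on significance alone. The 20% to 50% figures therefore describe one possible reading, and d = 0.8 lies almost at the maximum of 2p(1 − p).

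Nor is diagnosis absent from every comparison. It is listed among the patient-related data, and those are compared by dysphagia status and by anaesthesia group. Read together, these passages do give a stroke/TIA comparison on dysphagia, and they would show an imbalance of diagnosis between anaesthesia groups. Only the first two objectives literally refer to both cohorts, and that wording may simply describe the population. The regression might include diagnosis, and a separate analysis plan could list its terms; the unlisted predictors are not counted here as an error.

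What remains is narrower. The article sets out its group comparisons and tests in some detail, and these are unadjusted. Showing an imbalance does not correct for it. Comparing diagnosis by dysphagia status does not show whether anaesthesia or duration acts alike in the two cohorts.

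**Conclusion.** The point holds as a gap between the objectives and the stated tests. The article leaves open whether effects are pooled or per cohort, and it names no diagnosis-adjusted effect and no difference in effect between cohorts. It does not establish that a false subgroup claim is planned.

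The size depends on the reading. Under crude pooling, the bias depends on an anaesthesia imbalance and a cohort difference that the article does not give; it is zero if either is absent. Under separate tests, discordant significance from identical effects would occur about 20% to 50% of the time for d from 0.3 to 0.8 at 13:12. A combined estimate has about 0.57/0.83 = 69% of the per-cohort half-width. No analysis of 50 patients will settle whether the cohorts differ, which argues for estimation and against a confirmatory interaction test.

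**What to change.** For each swallowing outcome, estimate the anaesthesia effect on all 50 patients with diagnosis as a factor, using a model suited to ordinal scores (for example proportional odds). Do the same for TEE duration. Name the diagnosis-adjusted common effect as the main estimate, and say so wherever an effect size is carried forward to plan the full-scale study. Report the cohort-specific effects and their difference with 95% CIs as descriptive estimates, not as an interaction test. State that no stroke/TIA difference will be inferred from separate p-values.

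The cost is a few sentences of analysis text. Diagnosis is already collected, and it can enter as a coded two-level factor so that the statisticians stay blinded. The downside is that the cohort difference will be visibly imprecise, at about ±1.14 SD or wider, which is what a sample of this size can honestly show.

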## Methods

The study is a prospective, single-blinded, controlled trial, designed in accordance with the SPIRIT reporting guidelines [29]. The study protocol outlines that both FEES and TEE will be performed on patients who provide informed consent to participate. Patients with acute ischaemic stroke or transient ischemic attack (TIA) that provided their consent to participate are included in the trial. The patient recruitment flow diagram is presented in Fig. 1.

**Fig. 1 Fig1:**
[figure not shown]
Patient recruitment flow diagram

### Study setting

The trial will be conducted at the University Medical Centre of the Justus-Liebig-University in Giessen (UKGM) through collaboration between the Departments of Neurology and Cardiology of the UKGM.

### Eligibility criteria

A total of 50 patients will be recruited from the UKGM stroke unit, comprising 25 with ischaemic stroke and 25 with TIA.

The inclusion criteria are (1) ischaemic stroke occurring no more than 7 days prior, confirmed by cranial computed tomography (cCT) or magnetic resonance imaging (MRI); (2) for TIA: presence of a perfusion deficit in cCT or clinical diagnosis of TIA by a physician with focal neurological deficits still persisting at the time of presentation; (3) indication for TEE in both groups; (4) written informed consent to participate.

Exclusion criteria include (1) pre-existing neurogenic dysphagia; (2) prior surgery or chemoradiotherapy for head and neck tumours; (3) cervical spine surgery; (4) thyroid gland surgery; (5) aphasia; (6) acute delirium; (7) lack of compliance; (8) lack of alertness; (9) dementia; (10) existing legal guardianship.

TEE will be performed by cardiologists from the Department of Cardiology at UKGM. FEES will be conducted by neurologists and/or speech and language therapists (SLT) from the Department of Neurology at UKGM.

Trial participants or authorized surrogates will be informed in detail and comprehensibly both in a written consent form as well as in a personal interview by the medical investigator from the Department of Neurology about the treatment method to be tested and the comparative method as well as about the nature, significance, risks and scope of the clinical trial.

